**Outcomes:**

The primary outcome is index-visit Lifestyle Readiness and Confidence to Change scores. Secondary outcomes include satisfaction with the clinic visit, intention to change specific lifestyle behaviors, and healthcare use outside the clinic at 30 days and 6 months, as assessed via record review. A 3–12-month follow-up survey will assess self-reported lifestyle changes and new diagnoses.

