## Materials and methods

This will be a randomized, controlled, unblinded, two-armed superiority clinical trial. The study will be conducted according to the Standard Protocol Items: Recommendations for Interventional Trials (SPIRIT) Checklist (see S5 Checklist SPIRIT Checklist). The study was approved by Trinity Health at Ann Arbor Institutional Review Board (IRB number: E-24–1117). The trial was prospectively registered in the Clinicaltrials.gov database (registration number: NCT06730737).

The study’s primary outcome will be the results from the Lifestyle Readiness to Change and Confidence to Change questionnaires, both of which use a *readiness ruler* (see S2 Appendix B) [12]. The intervention will include four primary prevention domains promulgated by the American College of Lifestyle Medicine: diet, exercise, sleep hygiene, and smoking cessation.

Secondary aims include:

1)To evaluate the ability to implement a preventive education strategy in the primary care clinic setting2)To assess the impact of age on willingness to change lifestyle behaviors3)To determine characteristics of those receiving the video concerning patient satisfaction, utilizing select Hospital Consumer Assessment of Healthcare Providers and Systems (HCAHPS) Survey questions, compared to the control group

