**Fig 1 pone.0322244.g001:**
[figure not shown]
Flowchart for the study process. Note that all videos will use the interactive format. Patients will not be video recorded.

The randomization module within Research Electronic Data Capture (REDCap) will be used to allocate the video intervention. Those randomized for the intervention will be asked if they are interested and willing to watch a video about the clinic visit and their health. Those who agree to watch will then interact with a video featuring lifestyle changes relating to diet, exercise, sleeping, and smoking and why they are important for one’s overall health. The media is interactive because it contains questions for the user to answer at different points within the video sequence. The control group will not watch the video.

The study includes two surveys: the first will be administered in the clinic, and the second will be a follow-up survey administered upon phone contact with consenting patients. Target follow-up is planned for 3–12 months following the initial visit.

Whether receiving the video intervention or not, all participants will have provided verbal consent to answer the questionnaires (see the included script at the heading of the initial survey instrument within S2 Appendix B). They will then fill out the questionnaire at the end of the video either alone, with the assistance of an accompanying relative, or with the assistance of a research team member to determine their stage of the transtheoretical model. A study identification number will be placed on the completed survey. The ID number and the patient’s identifying information will be noted in REDCap. Any patient who declines to participate will not have their patient health information (PHI) included in the study. The REDCap file containing the patients’ personally identifiable information will be kept on password-protected servers using the institution’s REDCap.

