### Study procedures

Research associates and/or research team members will screen for eligible patients using a screening form based on the inclusion/exclusion criteria mentioned above. Results will be analyzed at two stages: first, with the results of the questionnaires administered as part of the initial visit, and second, after concluding the 3–12 month follow-up survey. The consent, educational video, and questionnaire will all be conducted while the patient is in the waiting room, after the clinician (physician or advanced practice provider) has completed the initial patient encounter, or after the provider contact has been completed.

The patients will fill out the composite questionnaire. This questionnaire is designed with the following criteria: prioritize using validated tools capable of self-administration. The Readiness-to-Change questionnaire evaluates patient readiness to implement ten lifestyle behaviors based on a 5-point rating scale. A rating of 5 represents having no interest in the suggested lifestyle change, which is consistent with the precontemplation stage of the transtheoretical model (TTM). A rating of 4 means an interest in implementing the lifestyle change in the next few months (contemplation stage of the TTM). A rating of 3 represents having the plan to implement the lifestyle change within the next month (preparation stage of the TTM). A rating of 2 represents having already started the lifestyle change within the past few months (action stage of TTM). A rating of 1 means having maintained lifestyle behavior changes for over 6 months (maintenance stage of TTM). The Confidence-to-Change questionnaire evaluates patient confidence in implementing the same lifestyle behaviors as the Readiness-to-Change questionnaire. However, the Confidence-to-Change questionnaire is based on a 3-point rating scale. Ratings are as follows: 3-very confident, 2-somewhat confident, and 1-not very confident [12]. The Confidence-to-Change questionnaire addresses any barriers or hesitancy that may impact patient confidence in implementing better lifestyle behaviors. Additional questions will include measures of satisfaction taken from the HCAHPS, specifically addressing their practitioner and visit (S2 Appendix B).

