Sometime after the visit (target: 3–12 months later), they will receive a phone follow-up call, asking them if they have adopted any lifestyle changes since watching the video, among other inquiries (S3 Appendix C). We will use patients’ responses at this later stage (follow-up phase) to help determine how sustainable the preventive education intervention has been.

Randomized patients who participate in the study will receive the video intervention. In a previous pilot study, we investigated the impact of a simple instructional video on patients’ willingness to change in the emergency department setting [13]. The initial intervention was passive, requiring subjects to watch a video without interaction. The current study evaluates the practicality and impact of bringing a brief *interactive* educational video intervention to patients attending the primary care clinic visit.

All patients, including those randomized to “no video learning,” will be asked to complete a questionnaire. The questions will be administered orally or self-administered for those willing to participate using the tablet interface. Responses will be recorded using REDCap electronic data capture software and the related platform.

A sample size of approximately 350 was chosen based on feasibility and the expectation of sufficient power to detect moderate differences in readiness and confidence scores, guided by prior pilot study results. Due to the minimal risks in this study, a data monitoring committee is not considered necessary. An interim analysis will be conducted after 200 patients have been enrolled. It is anticipated that the total data collection will take six months. For those patients who agree to receive a call-back, contact will be attempted during the 3–12-month follow-up period. A research associate, a resident, or an attending physician will complete the follow-up by telephone or email correspondence with the subject. Up to 3 follow-up attempts will be made. Available follow-up data from the interactive electronic health record (EHR) will be obtained on all patients. The estimated time to view and interact with the video is approximately 10–15 minutes. The time required for responses to the survey component is estimated at 10–12 minutes.

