### Data and safety monitoring plan

The principal investigator (PI) is responsible for this project’s conduct and shall ensure that all work and services described, or incidental to those described, are conducted following accepted standards of medical practice. The PI and co-investigators will maintain all master subject lists, and all data collected will be maintained in a password-protected secure server and reviewed at regular intervals to ensure adherence to the investigational procedures outlined in the protocol.

The approved research team members will obtain information regarding the patient’s lifestyle and demographic habits. Data will be accepted from primary care clinic records and charts. Each data abstractor will use a pre-formulated data collection tool to enhance the uniformity of information. Statistical analysis for inter-observer variability will be conducted on a subset of duplicate charts to ensure the quality of the data abstracted and used for the study.

Meetings will be held at regular intervals to discuss data management, general IRB compliance, and other study aspects and to analyze the collected data. The PI will evaluate data quality and ensure that data evaluation is performed frequently. All data will be documented and retained in the study files.

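### The 3–12-month follow-up may be collected by staff who know the patient's arm and by-arm results, leaving secondary self-reported outcomes open to avoidable interviewer bias

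*Protocol article*

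**What the plan says.** - **Blinding.** Materials and methods: "This will be a randomized, controlled, unblinded, two-armed superiority clinical trial". The abstract also calls the trial non-blinded. Neither place exempts the follow-up assessor.
- **Who collects follow-up.** Study procedures: "A research associate, a resident, or an attending physician will complete the follow-up by telephone or email correspondence with the subject". Up to three attempts are allowed.
- **Mode.** Participant enrollment and screening describes "a follow-up survey administered upon phone contact with consenting patients", whereas Study procedures also allows email.
- **What is asked.** Study procedures describes the call as "asking them if they have adopted any lifestyle changes since watching the video". The abstract says: "A 3–12-month follow-up survey will assess self-reported lifestyle changes and new diagnoses".
- **What is analysed before follow-up ends.** Study procedures: "Results will be analyzed at two stages: first, with the results of the questionnaires administered as part of the initial visit"; the follow-up survey is the second stage. Also: "An interim analysis will be conducted after 200 patients have been enrolled". The Data and safety monitoring plan adds: "Meetings will be held at regular intervals to discuss data management, general IRB compliance, and other study aspects and to analyze the collected data".
- **How follow-up is analysed.** Statistical methods plans complete-case logistic regression on binary or categorical answers such as Yes, No or Don't Know.

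**The concern.** The answers at 3–12 months are what the protocol will use to judge whether the intervention's effect lasts. They are soft: a short spoken exchange decides whether a patient is recorded as Yes, No or Don't Know. A caller who knows that the patient saw the video, who perhaps showed it, or who has seen that the video arm scored better at the index visit, can prompt a little more or settle an unclear answer differently by arm. Such a caller can also pursue one arm harder within the three attempts. The planned regression compares recorded answers and cannot tell this from a treatment effect.

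The patient cannot be masked to having seen a video. The person asking the questions largely can be, and the plan does not use that option.

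**Working it through.** The point concerns conduct, and the protocol gives no figure to reproduce. The check is first textual and then an illustration.

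**Step 1. Can the same person run the visit and make the call?** Study procedures has research associates or team members screen patients. Participant enrollment and screening lets a team member help with the index questionnaire. Informed consent lets a team member start the video. Follow-up is then given to a research associate, a resident or an attending physician. The roles overlap and nothing separates them for a given patient.

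**Step 2. Can the caller know by-arm results?** Index-visit questionnaires are the first analysis stage, an interim analysis follows 200 enrolments, and team meetings analyse collected data. No passage withholds these results from callers. The access limits under Data confidentiality and storage, Participant privacy and HIPAA serve confidentiality, not masking.

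**Step 3. Would the call itself reveal the arm?** As described, the question refers to watching the video, which only the intervention arm is offered. A caller using that wording either knows the arm already or is likely to learn it from the reply.

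**Step 4. Which outcomes depend on the call?** Self-reported lifestyle changes and new diagnoses do. Readiness and confidence scores (primary) are taken at the index visit. Healthcare use at 30 days and 6 months comes from record review.

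**Step 5. Illustration of size.** Inputs:
- From the protocol: about 350 patients in two arms.
- Assumed: 1:1 allocation (175 per arm), 60–80% reached (0.6 × 175 = 105; 0.8 × 175 = 140), true adoption of 40% in both arms, two-sided 5% test, and a shift b of 5 or 10 percentage points in recorded Yes answers in the video arm.

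With p₁ = 0.40 + b, p₂ = 0.40 and p̄ = (p₁ + p₂)/2:
- OR = [p₁/(1 − p₁)] / [p₂/(1 − p₂)]
- SE₀ = √[2p̄(1 − p̄)/n] and SE₁ = √[p₁(1 − p₁)/n + p₂(1 − p₂)/n]
- Rejection probability = Φ[(b − 1.96·SE₀)/SE₁] + Φ[(−b − 1.96·SE₀)/SE₁]

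Odds ratios:
- b = 0.05: (0.45/0.55)/(0.40/0.60) = 1.23
- b = 0.10: (0.50/0.50)/(0.40/0.60) = 1.50

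Worked case, n = 105 and b = 0.05: SE₀ = 0.0682, SE₁ = 0.0681, so Φ(−1.229) + Φ(−2.696) = 0.110 + 0.004 = 0.113.

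| Reached per arm | No shift | 5-point shift | 10-point shift |
|---|---|---|---|
| 105 | 0.050 | 0.113 | 0.307 |
| 140 | 0.050 | 0.135 | 0.390 |

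Using the unpooled standard error throughout gives 0.114 and 0.310 (105 per arm) and 0.135 and 0.394 (140 per arm), so the choice of test hardly matters. Over wider assumptions (adoption 20–50%, 50–100% reached), the range is about 10–20% for a 5-point shift and 26–58% for a 10-point shift.

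**The case against.** The strongest reply is that this faults the article for silence. It openly declares an unblinded trial, so no masking claim is contradicted. Call assignment and database permissions are operational detail that may sit in a fuller document, and the follow-up instrument (S3 Appendix C) is not shown. Part of this stands: the defect is an avoidable weakness, not an error. But the point does not rest on silence alone. The article fixes who calls, declares no blinding without exception, describes the question by reference to the video, and schedules analyses before follow-up ends.

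A reader might infer that callers will know the arm, will have delivered the video to the same patient, or will have seen by-arm results. The documents do not say so; they only leave it open. Nor do they say that callers can view the allocation field in REDCap, or who chooses between telephone and email.

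Safeguards exist. Attempts are capped at three, loss to follow-up will be reported by arm, completers will be compared with non-completers, and health-record data are obtained on all patients. These limit unequal pursuit and make it visible. They do not detect biased elicitation among patients who are reached.

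The size calculation assumes the bias and then shows its effect. That is correct, and it says nothing about how likely such a bias is. It also covers adoption only, not new diagnoses.

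Finally, patients know their own arm, so masking the caller leaves self-report bias in place, and email replies involve less interviewer influence. Both stand.

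**Conclusion.** The concern holds in limited form. The plan allows staff who may know the arm and by-arm results to collect the self-reported follow-up outcomes, and so leaves open an interviewer bias that could be reduced cheaply. It affects secondary outcomes only.

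If callers shifted recorded adoption in the video arm by 5 points, a nominal 5% test would reject in about 11–14% of trials with no true effect; for 10 points, in about 31–39%. These figures depend entirely on assumed adoption, reach and size of bias, none of which the protocol gives. A reader might infer that the trial's main conclusion is at risk. It is not, because the primary outcome is collected at the index visit and healthcare use comes from record review. The change is worth making but is not essential to the primary analysis.

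**What to change.** In Study procedures:
1. Assign each follow-up contact to an existing team member who did not see that patient at the index visit.
2. Hide the randomization field from callers through REDCap user rights.
3. Give callers no by-arm results, from the first-stage analysis, the interim analysis or team meetings, until follow-up closes.
4. Ask both arms the same arm-neutral question, for example about changes *since your clinic visit*. Without this, masking would not hold.
5. Reconcile phone only (Participant enrollment and screening) with phone or email (Study procedures): set one mode order for both arms, and record mode and number of attempts.

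In Limitations and assumptions, which names only generalizability, add that participants know their arm, so self-report bias in the follow-up outcomes remains.

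The cost is a permissions setting and a few sentences. Three caller roles are already named, so new staff should not be needed. However, the study runs when team members are available, so call scheduling becomes less flexible, and team members who make calls must be kept out of by-arm discussion until follow-up closes.

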### Statistical methods

The study team members will collect demographic data upon registration to the patient’s clinic. Patients from ages 18–80 will be included in the study. After informed consent, patients will be randomized to either the intervention or the control arm of the study. Only the interventional arm will interact with the video using a provided computer tablet which focuses on lifestyle preventive education. Control patients will not receive a video and will go directly to the follow-up questionnaire. Hence, both groups will receive the follow-up survey from research team members.

The Demographic data includes age, sex, gender, race, and insurance status. The patient’s BMI, Charlson Comorbidity Index, smoking status, responses to the social influences of health questionnaires, phone number, and frequency of ED visits will be documented from the patient’s EHR. Their zip code will also be collected for geographic and socioeconomic status analysis (S1 Appendix A).

The study’s primary outcome is the readiness and confidence to change scores as a function of video exposure, measured on a continuous “readiness ruler.” [14].

Secondary outcomes will include readiness to change in specific domains, including exercise, smoking, diet, sleep hygiene, living an overall healthy lifestyle, satisfaction with the hospital, and satisfaction with the practitioner, dichotomized between those who watched the video and those who did not. Part of this data will be obtained directly from the patient’s medical record (S1 Appendix A).

We will collaborate with Michigan Data Analytics, which will provide large-scale data abstraction to assist with obtaining the Charlson Comorbidity Index (CCI) for participating subjects. The remaining data will be collected using the Readiness-to-Change and Confidence-to-Change Lifestyle Questionnaires, the Pittsburgh Sleep Quality Index (PSQI), and U.S. Governmental HCAHPS Patient Satisfaction Survey.

Descriptive statistics will be used to summarize baseline characteristics by study arm, including means and standard deviations for continuous variables and proportions for categorical variables. All analyses will follow the intention-to-treat principle.

Outcomes collected at the clinic visit (e.g., readiness to change and confidence to change) will be compared between intervention and control groups using ordinal logistic regression, appropriate for ordinal outcome variables. As these measurements are taken after randomization and intervention (where applicable), no pre-intervention baseline measures will be available.

Follow-up outcomes, including receipt of additional care, adoption of lifestyle changes, and overall well-being, are recorded as binary or categorical variables (e.g., Yes/No/Don’t Know) and will be analyzed using logistic regression models. Clinic visit scores may be included as covariates to assess their association with follow-up outcomes.

A complete-case approach will be used for all primary and secondary outcome analyses. Differences in loss to follow-up between study arms will be reported, and characteristics of completers and non-completers will be compared to assess potential attrition bias. Multiple imputation is not planned due to the structure of data collection involving a single follow-up time point.

Separate regression models will be used to analyze outcomes collected at the clinic visit and follow-up. Given the design of the study, which includes a single post-intervention follow-up and no pre-intervention baseline, repeated measures modeling will not be used in the primary analysis. Secondary analyses may include generalized estimating equations or other repeated measures approaches to assess the consistency of findings.

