**Methods and analysis:**

We will conduct a prospective, randomized, non-blinded clinical trial among adult patients presenting to a primary care clinic. Immediately after their appointment, participants will be randomized to receive either the interactive prevention video or usual care. The video maintains engagement through simple in-video questions and adapts content based on patient responses (e.g., skipping smoking cessation for non-smokers). After the encounter, all participants will complete surveys assessing readiness and confidence to initiate lifestyle change including a transtheoretical “readiness ruler.” Survey items will be drawn from validated instruments, including the Gillespie & Lenz Readiness and Confidence to Participate in Lifestyle Activities Surveys, the Pittsburgh Sleep Quality Index (PSQI), and select questions from the U.S. Hospital Consumer Assessment of Healthcare Providers and Systems (HCAHPS) Survey. Patients will be asked for medical record access and permission for follow-up contact.

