**Statistical plan and sample size:**

Analyses will follow intention-to-treat. Ordinal logistic regression will compare primary outcomes between arms, adjusting for Charlson Comorbidity Index, age, sex, gender, and prespecified predictors. Logistic regression will evaluate binary follow-up outcomes. Complete-case analyses will be used, and differential attrition will be reported. We plan to enroll approximately 350 patients.

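### The follow-up survey is analysed by complete case, and multiple imputation is rejected for a reason that does not hold

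*Protocol article*

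**What the plan says.** All the provisions cited here are in the protocol article.

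- Statistical methods sets one rule for everything: "A complete-case approach will be used for all primary and secondary outcome analyses". The reason for not imputing follows: "Multiple imputation is not planned due to the structure of data collection involving a single follow-up time point".
- The same section plans to report loss to follow-up by arm, and says that "characteristics of completers and non-completers will be compared to assess potential attrition bias". It names no corrected estimate and no sensitivity analysis for missing data. It also states: "All analyses will follow the intention-to-treat principle".
- It allows clinic-visit scores as optional covariates in the follow-up models, in order to study their association with later outcomes.
- Under Participant enrollment and screening, and under Study procedures, the later survey goes only to patients who agree to be contacted. On effort: "Up to 3 follow-up attempts will be made".
- Study procedures also plans to obtain later record data for all patients. The Abstract (Outcomes) adds record review of outside healthcare use at 30 days and 6 months.
- The Abstract describes the primary model as "adjusting for Charlson Comorbidity Index, age, sex, gender, and prespecified predictors". On permissions it says: "Patients will be asked for medical record access and permission for follow-up contact".

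**The concern.** The number of follow-up times has no bearing on whether a missing answer can be imputed. What matters is whether the trial holds variables that predict the answer or the non-response. Here it does: both index-visit scores in both arms, comorbidity, BMI, smoking status, social factors, emergency visits, and later record data that do not depend on the patient answering the telephone.

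Non-response to the survey is likely, because contact needs agreement and stops after three tries. Those who agree and answer may well be the more motivated. If that selection works differently in the two arms, for example because the video engages some patients and tires others, the complete-case contrast mixes the effect of the video with the effect of who answered. The survey is what the protocol relies on to judge whether the education has a lasting effect, so that conclusion is at stake.

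Describing attrition does not repair this. Equal response rates by arm can hide different kinds of responder, and a table of completers against non-completers leaves the estimate unchanged.

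**Working it through.** **The plan's own figure.** The only relevant number is the sample size: "A sample size of approximately 350 was chosen based on feasibility and the expectation of sufficient power to detect moderate differences". No alpha, power, effect size, SD, allocation ratio or dropout rate is given, so 350 cannot be reproduced. Assuming 1:1 allocation, two-sided 5% and 80% power, the detectable standardised difference is (1.960 + 0.842) × √(2/n per arm). With 175 per arm this is 0.30 SD.

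**Hand example for the survey (all inputs assumed).** Half of each arm has high index-visit readiness. Adoption is 60% if readiness is high and 30% if low, in both arms. The true rate is therefore 0.5 × 0.6 + 0.5 × 0.3 = 45% in each arm, a true difference of 0.

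Complete-case rate = Σ(share × response × adoption) / Σ(share × response).

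| Response, high/low readiness | Overall response | Complete-case adoption |
|---|---|---|
| 60%/60% (control) | 60% | (0.18 + 0.09)/0.60 = 45% |
| 80%/40% (video) | 60% | (0.24 + 0.06)/0.60 = 50% |
| 70%/50% (video, milder) | 60% | (0.21 + 0.075)/0.60 = 47.5% |

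The false benefit is 5 points, or 2.5 points in the milder case. Overall response is 60% in both arms each time, so the planned report of loss by arm would show no difference. If both arms respond at 80%/40%, both show 50% and the false difference is 0. Imputing within arm from readiness restores 60% and 30% in the two strata, and so 45% in each arm.

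**Simulation (all inputs assumed).** 350 patients, 175 per arm, 1,000 runs. The index score has SD 1. The logit of adoption is −0.4 + score. The logit of response is 0.4 + score, with the score acting either in the video arm only or in both arms. Where there is a true effect, the video raises the score by 0.3 SD. Imputation used 10 data sets, with arm, score, age and arm-by-score as predictors. Entries are risk differences.

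| Case | Response, control/video | Full data | Complete case | Imputation |
|---|---|---|---|---|
| No effect, score drives response in video arm only | 60%/58% | −0.001 | 0.069 | 0.000 |
| True effect, score drives response in video arm only | 60%/64% | 0.060 | 0.122 | 0.061 |
| True effect, same dependence in both arms | 58%/64% | 0.059 | 0.052 | 0.059 |

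In the first case, complete case rejected the null in 18.0% of runs at a nominal 5%, and imputation in 5.7%. In the third, the bias is small and power is 11.7% against 14.8%.

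**Optional adjustment for clinic scores.** In the two true-effect cases, adoption depends on the arm only through the index score. The whole effect is about 0.06, yet at a given score it is zero. A model that conditions on the score would target that zero.

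**Primary outcome.** If, as an assumption, 10% lacked a chart covariate, 350 would fall to 315 (157.5 per arm). The detectable difference would rise from 0.2995 to 0.3157 SD, that is, from 0.30 to 0.32.

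**The case against.** The strongest reply has four parts.

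- **The bias is constructed.** It needs response to depend on readiness differently by arm. With equal dependence, the hand example shows no bias and the simulation only 0.052 against 0.059. The document states no response rate, so heavy loss is an inference. This stands: the figures illustrate a mechanism and do not predict this trial.
- **The data are not discarded.** A reader might infer that the index-visit scores go unused. The document does not support that, since they are allowed as covariates, and in the hand example stratifying on readiness gives 60% v 60% and 30% v 30%, which removes the false difference. But this use is optional and aimed at association. The scores are measured after the intervention, so adjusting for them changes the effect being estimated.
- **The primary analysis is barely touched.** A reader might infer that many completed questionnaires would be deleted for want of a comorbidity index. The text does not support this. Consent precedes randomisation, later record data are planned for all patients, and nothing says that a patient who refuses record access stays in the trial. The questionnaire is completed at the same visit. With no pre-intervention score, imputing a missing primary outcome would add little. The 10% above is an assumption, and even then the change is small.
- **Complete case is compatible with intention-to-treat.** A reader might see a contradiction. Analysing observed patients in their randomised arm is common under that label, and the plan discloses it. The tension is real, but it is not an error on its own.

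A missing SAP does not answer the point. The article itself fixes the method and gives the faulty reason.

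**Conclusion.** The concern holds for the 3–12-month survey outcomes. The reason for rejecting imputation is wrong, non-response is likely by design, and the plan has no analysis that corrects for it or tests sensitivity to it. The size is unknown: nil to 5 percentage points in the hand example, and about 6 to 7 points in the simulation when response depends on readiness in one arm only. All of these rest on assumed response and adoption rates. Imputation removes the bias in these examples because, by construction, the data are missing at random given arm and index score. That cannot be taken for granted in the trial.

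The point does not extend with the same force to the other outcomes. Index-visit measures do not depend on the call-back, and outside healthcare use comes from records. Because the survey is secondary, this is a change worth making rather than a threat to the primary result.

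**What to change.** - Delete the sentence that rests the decision on having one follow-up time.
- Analyse the follow-up survey outcomes by multiple imputation done separately by arm, using the index-visit readiness and confidence scores, baseline variables and record data, including later record data. Leave the clinic-visit scores out of the model that estimates the treatment effect.
- Keep complete case as a sensitivity analysis. Add one for data missing not at random, for instance by shifting the imputed adoption rate among non-responders over a stated range that may differ by arm.
- For the primary outcome, as a minor safeguard, keep every randomised participant with an observed questionnaire, and fill any missing baseline covariate by mean imputation or a missing indicator.
- Keep the planned attrition tables.

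The cost is a few sentences and modest programming, with no new data. The downside is that the main survey estimate will rest on missing at random given the chosen predictors, which is why the sensitivity analysis for departures belongs with it.
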